### Plans to promote participant retention and complete follow-ups

Participant retention and follow-ups are expected to be easy in this study because patients are observed only during their hospitalization in the ICU.

### Data management

Patient data are stored in raw medical records at each hospital and anonymized EDC for at least five years. Changes in EDC are preserved with a log showing the information of who and when they are changed.

### Confidentiality

All patient data are anonymized in the EDC system. Only study physicians, who were given the original ID and password, access EDC and solely input data on patients at their facility. The statistician and central monitor have exclusive access to all participants’ data.

### Plans for collection, laboratory evaluations, and the storage of biological specimens for genetic and molecular analyses in this trial/future use

If we obtain additional consent from each patient, we will collect plasma, whole blood, and fecal samples on Days 0, 3, and 7 and store them at −80°C. These samples will be used to perform additional analyses on lipid and protein metabolism and to examine the effects of diarrhea on nutrient metabolism in severe disease.

### Statistical methods

#### Statistical methods for primary and secondary outcomes.

Statistical analyses are performed using an intention-to-treat analysis with a full analysis set (FAS) and safety analysis set (SAS). FAS is defined as all subjects without violations of the main eligibility criteria (selection and exclusion criteria) or conflicts with discontinuation and dropout criteria. SAS is defined as all subjects who received the study treatment. The efficacy analysis is performed with FAS. The safety analysis will be performed with SAS. No statistical methods are used to handle missing data (e.g., multiple imputation).

Frequencies will be calculated for binary data, including the incidence of diarrhea, the rate of EN failure, and the survival rate on Day 28. Continuous variables assumed to follow a normal distribution, such as age, height, and weight, will be presented as means and standard deviations. Variables not assumed to follow a normal distribution, such as ICU stay, hospital stay, and ventilator days, will be reported as medians and interquartile ranges. Pearson’s chi-square test will be employed to compare groups for the primary endpoint. In principle, a two-tailed test is conducted with a significance level of 5% and CI of 95%. To examine the interaction effect, subgroup analyses will be performed with the following subgroups: sex, age (<70 years old/ ≥ 70 years old), BMI (≤20/ 20 < BMI ≤ 30/ ≥ 30), SOFA scores (less than 2 points in one or more items/others) [12], and disease category (infectious disease, heart failure, respiratory failure, stroke, renal or metabolic diseases, postoperative, post-cardioplumonary resuscitation, trauma, other).

Regarding secondary endpoints and adverse events, between-group comparisons for binary outcomes will be analyzed using confidence intervals for differences in population proportions, while continuous outcomes will be analyzed by confidence intervals in means or medians. Additionally, as a post-hoc analysis, a subgroup analysis will be conducted based on the above results.

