#### Interventions for each group with sufficient detail to allow replication, including how and when they will be administered.

The SPIRIT Figure is shown in Fig 1 and the study outline is in Fig 2. After obtaining written consent from potentially eligible patients, the necessary tests will be conducted to confirm eligibility. The use of test data obtained before consent will be allowed. EN will be started at the discretion of the physician in charge according to medical indications. There is no time limit between enrollment and the initiation of EN, however, there are minimal practical barriers to starting EN in the enrolled patients, and efforts to align enrollment timing with EN initiation are encouraged in order to minimize cases where EN could not be commenced post-enrollment. Therefore, EN is expected to be initiated within 24 hours.

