### Criteria for discontinuing or modifying allocated interventions

If a participant does not meet eligibility after enrollment and prior to administration of the study nutrient, the intervention will be terminated and no study nutrient will be administered.

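### The efficacy analysis is called intention-to-treat, but its only analysis set removes enrolled patients on grounds that can be decided after open allocation

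*Protocol article*

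**What the plan says.** The section on statistical methods for primary and secondary outcomes states the principle first: "Statistical analyses are performed using an intention-to-treat analysis with a full analysis set (FAS"). It then defines that set: "FAS is defined as all subjects without violations of the main eligibility criteria (selection and exclusion criteria) or conflicts with discontinuation and dropout criteria". It ties all efficacy results to it: "The efficacy analysis is performed with FAS". On gaps in the data it says "No statistical methods are used to handle missing data (e.g., multiple imputation"). The safety set is everyone who received study treatment. No other efficacy set, and no supporting analysis of all randomised patients, is named.

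Four other places bear on how the definition works:

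- Criteria for discontinuing or modifying allocated interventions. The rule given there reads: "If a participant does not meet eligibility after enrollment and prior to administration of the study nutrient, the intervention will be terminated". Such a patient gets none of the trial formula. This is the only discontinuation criterion printed in the article.
- Interventions for each group: "There is no time limit between enrollment and the initiation of EN". The same paragraph expects feeding to begin within 24 hours and encourages sites to align enrolment with the start of feeding, in order to "minimize cases where EN could not be commenced post-enrollment".
- Sequence generation and implementation: the allocation appears when the physician enters the patient on the EDC site.
- Blinding: participants, care providers, outcome assessors and data analysts all know the arm.

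**The concern.** Intention-to-treat means that every randomised patient is analysed in the allocated arm. A set that drops patients for eligibility violations, or under discontinuation and dropout criteria, does not meet that description, so the label and the definition contradict each other within a few lines.

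This is more than a naming matter, because of when and by whom the exclusions can be made. Enrolment on the EDC reveals the arm. After that, a patient may be found ineligible before feeding starts, and one exclusion criterion leaves suitability to the physician's judgement. Nothing in the article requires these decisions to be made, or checked, by someone unaware of the arm. If patients at higher or lower risk of diarrhea are removed more readily from one arm, the groups in the primary chi-square test are no longer the groups that randomisation created. With no handling of missing data and no all-randomised analysis, the planned results would not reveal it.

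**Working it through.** **Inputs from the article.** Control risk 50%, treatment risk 30%, two-sided 5%, 80% power, Pearson chi-square, 93 per group, raised to 100 per group for dropouts (Sample size).

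**The plan's own figure.** With pooled variance under the null,

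n = [1.960·√(2·0.40·0.60) + 0.842·√(0.50·0.50 + 0.30·0.70)]² / 0.20² = (1.358 + 0.571)² / 0.04 ≈ 93 per group.

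This matches. The target of 100 equals 93/(1 − 0.07), an implied allowance of 7% (the article states no rate). The sample size is not in error; the problem is the analysis set.

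**Effect of exclusions when there is no true effect.** The article gives no exclusion rates, so the following are assumptions: 50% risk in both arms, 100 per arm, exclusions in the treatment arm only. Let d be the share excluded and q the diarrhea risk among those excluded. The rate left in the efficacy set is

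p′ = (0.50 − d·q)/(1 − d).

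With δ = 0.50 − p′, the chance of a significant result is Φ((δ − 1.96·se₀)/se₁) + Φ((−δ − 1.96·se₀)/se₁). Here se₀ is the pooled and se₁ the unpooled standard error, with 100 and 100(1 − d) patients.

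Worked case, d = 7%, q = 100%: p′ = 0.43/0.93 = 0.462; δ = 0.038; se₀ = 0.0720; se₁ = 0.0719; Φ(−1.44) + Φ(−2.48) = 0.075 + 0.007 = 0.082.

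| Excluded, treatment arm only | q = 50% | q = 75% | q = 100% |
|---|---|---|---|
| 5% | 0 points, 5.0% | 1.3 points, 5.4% | 2.6 points, 6.6% |
| 7% | 0 points, 5.0% | 1.9 points, 5.8% | 3.8 points, 8.2% |
| 10% | 0 points, 5.0% | 2.8 points, 6.7% | 5.6 points, 11.9% |

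Each cell gives the spurious benefit and the type I error. If q is below 50%, the sign reverses and the treatment looks worse. If 7% are excluded from both arms but selectively (75% with diarrhea in treatment, 25% in control), the figures are 3.8 points and 8.1%.

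**Power when all 100 per arm are analysed.** At 50% v 30% it is 82.8%. If a share of the treatment arm keeps the 50% control risk (assumption), the treatment rate is 0.30 + share × 0.20:

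- 5%: rate 0.310, power 78.6%
- 7%: rate 0.314, power 76.7%
- 10%: rate 0.320, power 73.8%

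**The case against.** The best case for the plan is that the definition may do little harm. The one discontinuation criterion printed concerns patients found ineligible before receiving any study formula, and such an exclusion cannot reflect how the formula was tolerated. Removing patients who were ineligible at baseline is a recognised and often defensible departure, provided it is judged without knowledge of arm and outcome. The expected start within 24 hours also shortens the window in which eligibility could be reconsidered. All of this stands, and it limits how much bias should be presumed.

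It also rules out two stronger readings that a reader might infer:

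- **That patients are removed because feeding was stopped for diarrhea.** The article calls diarrhea a common cause of stopping enteral nutrition, so the inference is tempting. But it does not say that stopped feeding is a discontinuation or dropout criterion. EN failure on Days 3 and 7 and the duration of EN are secondary outcomes, and efficacy is analysed in this same set. They could hardly be estimated if such patients were dropped. A patient stopped for diarrhea that meets the Bristol definition within the 3 days has also already reached the primary endpoint.
- **That the set is a per-protocol set.** The definition sets no condition on formula received, amount, or days of feeding. On the printed criterion it is closer to a modified intention-to-treat set of eligible patients. Which it is depends on criteria not shown.

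The objection does not remove the contradiction. The article itself states the definition, the dropout clause is open-ended as printed, and no judgement blind to arm is provided for. A fuller document could explain the criteria, but the published definition would still not be intention-to-treat.

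**Conclusion.** The point holds. The efficacy set as defined is not intention-to-treat, it is the only efficacy set named, and its exclusions can be decided after allocation by people who know the arm. The primary comparison can therefore be biased.

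How much, and in which direction, cannot be settled from the article. If exclusion is unrelated to outcome there is no bias. Under the assumed one-arm exclusion of 7%, the spurious benefit is about 2 to 4 points and the type I error 5.8% to 8.2%. The 7% is borrowed from the general dropout allowance and is not a forecast of exclusions.

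A reader might go further and place seven exclusions per arm at the extremes, turning 50/100 v 30/100 (20 points) into anything from 43/93 v 30/93 (14.0 points) to 50/93 v 23/93 (29.0 points). Those are arithmetic limits. They require every excluded patient in one arm to have diarrhea and none in the other, and nothing in the article suggests that pattern.

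The correction is worth requiring because the set defines the primary result and the change is cheap.

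**What to change.** Before the data are analysed, amend the analysis-set text as follows:

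1. Define the primary efficacy set as all randomised patients, analysed in the allocated arm.
2. Allow exclusion only for withdrawal of consent to data use, or for ineligibility shown by data recorded before randomisation and judged without knowledge of arm or outcome.
3. State how patients who were never fed, or who lack a 3-day diarrhea assessment, are counted, with the same rule in both arms. This is needed because the primary endpoint is timed from administration of the study formula, so a never-fed patient has no defined observation window.
4. Keep the present definition as a sensitivity analysis, with its discontinuation and dropout criteria listed, under a name other than intention-to-treat.

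The cost is wording, plus some dilution of the estimate by patients who did not follow their allocation. At 100 per arm, power is 82.8% with no dilution and about 76.7% if 7% of the treatment arm keeps the control risk (assumption). In that case 80% power would need 109 per arm.

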**Methods:**

A protocol for planning a multicenter, parallel-group, open-label RCT is described herein. Enrolled patients are those ≥18 years of age with the indication of enteral nutrition by gastric access. Overall, 200 patients will be randomized into an intervention group administered an enteral formula containing low-methoxy pectin and a control group administered an enteral formula with similar components, but without pectin at a ratio of 1:1. Each enteral formula will be administered for 3 days or longer. There are no restrictions on other treatments. The primary outcome is the incidence of diarrhea as defined by Bristol Scale 5, 6, or 7. Secondary outcomes include the rate of EN failure, the survival rate, the lengths of ICU and hospital stays, and nutritional endpoints.

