### Trial design

The LOME-PECT trial is a multicenter, parallel-group, open-label RCT. The study is Specified Clinical Research under the Clinical Trials Act in Japan. This clinical study will enroll 200 adult patients admitted to the ICU. The study period is between March 08th, 2024 and March 31st, 2028. The recruitment started on 26 June 2024 and will continue until 31 March 2025.

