### Sample size

Based on our previous retrospective study, we estimated the incidence of diarrhea in this study [9]. The incidence of diarrhea in the control group using GLUCERNA® REX was estimated to be 50%, while that in the treatment group using HINEX® RENUTE was 30%. By applying Pearson’s chi-square test to the predicted incidence of diarrhea at a two-sided significance level of 5%, the number of cases required to maintain 80% power was calculated to be 93 in each group. In consideration of some dropouts, the target number of cases was set at 100 in each group, for a total of 200 cases.

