### Assignment of interventions: allocation

#### Sequence generation and implementation.

Block randomization is performed using electronic data capture (EDC). The EDC site automatically generates a random sequence in each hospital; therefore, stratification is performed only for the facilities. Study physicians include participants on the EDC site, on which their allocation and assigned procedure are rapidly noted.

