### Data collection and management

#### Plans for the assessment and collection of outcomes.

The outcomes and baselines of all participants are collected and assessed on EDC. All data collection forms were newly created for use only in this study by TXP Medical Corp. Japan.

Baseline data to be collected consist of background characteristics, disease category, Sequential Organ Failure Assessment (SOFA), nutrition screening based on the Malnutrition Screening Tool (MUST), laboratory test, and gastrointestinal symptoms including Bristol scale [11–13]. Details of these items are shown in S1 Table. Descriptive statistics will be calculated to summarize these variables. Between-group inferential statistical comparisons will not be conducted, as these analyses are intended for descriptive purpose only.

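### Randomisation is stratified by hospital but the primary chi-square test is not; if hospitals differ in diarrhea rate the test is somewhat conservative, and a stratified analysis would match the design at almost no cost

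*Protocol article*

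**What the plan says.** - **Design.** The protocol article, under Trial design, describes a multicentre trial: "The LOME-PECT trial is a multicenter, parallel-group, open-label RCT". Under Sequence generation and implementation, allocation is in blocks and the EDC system "automatically generates a random sequence in each hospital; therefore, stratification is performed only for the facilities". Hospital is therefore the only stratification factor. The Abstract gives the allocation ratio as 1:1.
- **Primary analysis.** Under Statistical methods for primary and secondary outcomes, Pearson's "chi-square test will be employed to compare groups for the primary endpoint". No stratum or covariate is named.
- **Sample size.** The Sample size section uses the same test: 50% v 30%, two-sided 5%, 80% power, 93 per group, raised to 100 per group.
- **Not given.** The text at hand states neither the number of hospitals nor how far diarrhea rates vary between them.

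**The concern.** The analysis does not follow the randomisation. Blocking within hospital keeps the arms balanced in every hospital, so differences between hospitals largely cancel out of the treatment comparison. An unstratified chi-square still counts those differences as random error. If hospitals differ, its standard error is too large, its type I error falls below the nominal 5%, and it has less power than a hospital-stratified test on the same patients.

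Hospital differences are plausible here. The start of feeding and the energy target are left to the physician, and treatment other than nutrition is unrestricted. The Introduction names antimicrobial duration and suppository use as risk factors for diarrhea, and the endpoint is a stool score given by local nursing staff. At stake is a modest amount of precision that the design has already secured and the analysis does not use. A false-positive risk is not at stake.

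**Working it through.** **Step 1. Reproduce the plan's figure.** Inputs from the Sample size section: p0 = 0.50, p1 = 0.30, mean 0.40, two-sided 5%, 80% power.

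n per group = [1.960·√(2·0.40·0.60) + 0.842·√(0.50·0.50 + 0.30·0.70)]² / 0.20²
= [1.960·0.6928 + 0.842·0.6782]² / 0.04
= (1.358 + 0.571)² / 0.04 ≈ 93.

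This matches the protocol. At 100 per group, z = (0.20·√100 − 1.358) / 0.678 = 0.947, which is 82.8% power. The crude test therefore delivers the planned power on the protocol's own rates.

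**Step 2. Why ignoring hospital makes the test conservative.** Let p_h be the rate in hospital h and p the overall rate. The total variance splits as

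p(1−p) = mean of p_h(1−p_h) + variance of p_h.

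With 1:1 blocks within hospital, essentially only the first term contributes to the true error of the comparison. The chi-square uses both. The excess is zero if hospitals do not differ and grows with their spread.

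**Step 3. Size.** The simulation used 4,000 trials per setting, 200 patients, equal-sized hospitals, blocks of 4, and normally distributed hospital effects on the logit scale. Marginal rates were held at 50% v 30%, or 40% in both arms under the null. The numbers of hospitals, their SDs and the block size are assumptions. Power and type I error are shown for 5 / 10 / 20 hospitals, and differences come from unrounded values.

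| Hospital SD (logit) | Power, chi-square (%) | Power, CMH (%) | Difference (points) | Type I error, chi-square (%) |
|---|---|---|---|---|
| 0 | 84.2 / 83.2 / 83.6 | 84.2 / 83.1 / 82.3 | 0 / −0.1 / −1.4 | 4.7 / 5.4 (10 and 20 hospitals) |
| 0.3 | 84.0 / 83.5 / 82.8 | 84.1 / 83.3 / 82.3 | +0.1 / −0.2 / −0.5 | 4.9 / 5.0 / 4.8 |
| 0.6 | 83.4 / 84.3 / 83.6 | 84.4 / 85.5 / 85.1 | +1.0 / +1.2 / +1.6 | 4.5 / 4.6 / 4.2 |
| 1.0 | 86.1 / 85.5 / 85.7 | 88.9 / 89.3 / 88.8 | +2.8 / +3.8 / +3.2 | 4.1 / 3.1 / 3.3 |

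To read the SDs: around a 50% rate, plus or minus one SD is 1/(1+e^±SD). That is about 43-57% at 0.3, 35-65% at 0.6 and 27-73% at 1.0.

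Under the null the crude standard error exceeded the true one by about 2-3% at SD 0.6 and 7-10% at SD 1.0. For example, with 10 hospitals and SD 1.0 it was 0.0684 against 0.0625, a ratio of 1.095.

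**Step 4. Simulation error.** Each power figure has a standard error of √(0.84·0.16/4000) = 0.6 point, and each type I error √(0.05·0.95/4000) = 0.3 point. The 3.1% should be read with that in mind. A separate simulation with 20,000 trials per setting, at SD 1.0, gave crude type I error of 3.8% (5 hospitals) and 3.9% (10 hospitals), against 5.0% and 5.3% for CMH. Power was 85.2% v 88.3% and 85.5% v 88.8%. At SD 0.5 the gain was under 1 point.

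**Step 5. In patients.** The equivalent sample-size ratio is [(1.960 + z_stratified)/(1.960 + z_crude)]², where z is the normal quantile of the power. With 10 hospitals and SD 0.6 (84.3% v 85.5%) it is (3.018/2.967)² = 1.03. At SD 1.0 (85.5% v 89.3%) it is (3.203/3.018)² = 1.13.

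**The case against.** The strongest objection is that the loss is conditional. Nothing in the document measures hospital variation. The formula, route, starting rate and rate escalation are standardised, and at least two nurses who know the scale assess the stools. With little variation nothing is gained, and with 20 small hospitals and no hospital effect the stratified test was about 1 point worse. All of this stands, and it limits the point to a modest, conditional gain. The 37.7-73.8% range in the Introduction does not settle the matter, because it describes critically ill patients in general and not a spread between hospitals.

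A second objection is that an unseen SAP may specify more. The protocol does not leave the primary test open, however. It names one, so a stratified test in the SAP would have to be reconciled with it.

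A reader might infer three stronger things that the document does not support:

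- **That planned power is lost.** It is not. The trial was sized for this same chi-square, and the loss is only relative to a stratified analysis.
- **That leaving out the baseline Bristol score also makes the error bars too wide.** The score is collected ("laboratory test, and gastrointestinal symptoms including Bristol scale") but is not a stratification factor, so omitting it leaves the crude standard error valid. With an assumed prognostic covariate and no hospital effect, the simulated ratio of crude to true standard error was about 1.0. Adjustment could add precision, but the exclusion of scores of 5 or more confines the baseline score to 1-4, and its prognostic value is not documented.
- **That SOFA is collected and never used.** It is a prespecified subgroup factor.

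**Conclusion.** The point holds in a limited form. Hospital is the sole stratification factor, and the stated primary test ignores it. If hospitals differ, the test is conservative and its standard error somewhat too large. Across 5 to 20 equal-sized hospitals, the change in power from stratifying runs from about −1 to +4 points. It is about nil at a logit SD of 0 to 0.3 (slightly negative with many small hospitals), 1 to 1.6 points at 0.6, and about 3 to 4 points at 1.0. The larger figures need wide hospital differences that the document neither states nor excludes. Type I error is not inflated, and the 80% target is met either way. This is a worthwhile and nearly free improvement. It does not threaten the validity of the result.

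**What to change.** Before data are analysed, state in the protocol and SAP that:

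1. The primary test is a Cochran-Mantel-Haenszel test stratified by hospital, two-sided 5%.
2. The effect measure is the Mantel-Haenszel risk difference with its 95% CI. It is Σ w_h(p_1h − p_0h)/Σ w_h with w_h = n_1h·n_0h/(n_1h + n_0h), and the variance estimator should remain valid with many small strata.
3. Very small hospitals are pooled by a fixed rule based on total enrolment, set without reference to outcomes. A hospital with patients in only one arm would otherwise contribute nothing.
4. The crude chi-square is kept as a sensitivity analysis.

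Adjustment for baseline covariates is at most an optional, prespecified supportive analysis. With about 100·0.50 + 100·0.30 = 80 expected events and an unknown number of hospitals, a logistic model with hospital terms and several covariates could be sparse.

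The trial is open-label and its analysts are unblinded, so the change should be dated and recorded before any comparison by arm. The cost is a paragraph of wording and a few lines of code. It needs no new data and no change to the sample size.

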#### Secondary outcomes.

Secondary outcomes are (1) the Bristol Scale, the presence or absence of diarrhea (≥200 g/day or 300 ml/day) and watery diarrhea (Bristol Scale 7) on Days 1, 2, and 3; (2) the occurrence of diarrhea (defined by Bristol Scale 5–7) in the first week; (3) the rate of EN failure on Days 3 and 7; (4) the duration of EN; (5) the daily doses of energy (kcal/day) and protein (g/day) for EN and PN during the first 7 days; (6) the survival rate on Day 28; (7) the length of ICU stay; (8) the length of hospital stay; (9) ventilator days; (10) nutritional endpoints: white blood cells, total lymphocyte count, C reactive protein, albumin, transthyretin, cholesterol (total, low density lipoprotein, and high density lipoprotein) and triglycerides on Days 7 and 14; (11) the Barthel index on Day 28; (12) the occurrence of adverse events, including enteral feeding intolerance and infectious complications.

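### Day 7 and Day 14 laboratory outcomes are compared without their baseline values, which costs precision; stay, ventilation and Barthel comparisons need a supportive analysis in case mortality differs

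*Protocol article*

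**What the plan says.** The section on statistical methods for primary and secondary outcomes gives one rule for all continuous secondary endpoints: "continuous outcomes will be analyzed by confidence intervals in means or medians". It names no baseline covariate and no stratification factor. On description it adds: "Variables not assumed to follow a normal distribution, such as ICU stay, hospital stay, and ventilator days, will be reported as medians and interquartile ranges". On incomplete data it says: "No statistical methods are used to handle missing data (e.g., multiple imputation".

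The section on the assessment and collection of outcomes lists, as baseline data, "nutrition screening based on the Malnutrition Screening Tool (MUST), laboratory test, and gastrointestinal symptoms including Bristol scale". The use it gives them is this: "Descriptive statistics will be calculated to summarize these variables". The individual analytes are in S1 Table, which is not shown.

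The list of secondary outcomes includes blood markers and lipids on Days 7 and 14, ICU and hospital stay, ventilator days, the Barthel index on Day 28 and survival on Day 28. Under sequence generation, hospital is the only stratification factor.

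**The concern.** Two features of the stated comparison raise questions.

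The first is precision. Laboratory values in ICU patients differ widely at entry, and a later value usually correlates with the entry value. Comparing raw Day 7 or Day 14 values leaves that between-patient variation in the error term. Data that could remove it appear to be collected but are used only to describe the sample. The cost is wider intervals than the same patients could give.

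The second is interpretation when patients die. A patient who dies early contributes a short stay and few ventilator days if the observed values are used, and has no Barthel index on Day 28. If one arm had more deaths, its stay could look better for that reason alone, and its Barthel comparison would rest on a more selected group of survivors.

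**Working it through.** **The plan's own figure.** The only numerical result in the plan is the sample size for the primary outcome: 50% against 30%, two-sided 5%, 80% power.
- n per arm = [1.960·√(2·0.40·0.60) + 0.842·√(0.50·0.50 + 0.30·0.70)]² / 0.20² = 93, as stated.
- Power at 100 per arm is 82.8%.

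Nothing below changes this, because it concerns secondary outcomes only.

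**Baseline adjustment.** Inputs: 100 patients per arm (Sample size section) and a baseline-to-follow-up correlation r. The documents give no r, so 0.3, 0.5 and 0.7 are assumed. Relative to the raw comparison, ANCOVA on the baseline value multiplies the variance by 1 − r² and the interval width by √(1 − r²). The standardised difference detectable with 80% power is (1.960 + 0.842)·√(2/100 · (1 − r²)); it is 0.40 without adjustment.

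| r (assumed) | variance factor | width factor | narrower by | detectable difference (SD) |
|---|---|---|---|---|
| 0.3 | 0.91 | 0.954 | 5% | 0.38 |
| 0.5 | 0.75 | 0.866 | 13% | 0.34 |
| 0.7 | 0.51 | 0.714 | 29% | 0.28 |

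At r = 0.5 the gain equals 100/0.75 = 133 patients per arm analysed without adjustment. These figures assume complete values, so they show relative gain and not the precision the trial will reach.

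**Death and length of stay.** The documents give no mortality rate and no stay distribution, so all inputs here are assumed. Stay is lognormal with log-SD 0.8, median 10 days in survivors and 5 days in patients who die, identical in both arms. The formula has therefore no effect on stay in either group. With mortality m, the raw median x solves

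(1 − m)·Φ[ln(x/10)/0.8] + m·Φ[ln(x/5)/0.8] = 0.5.

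- m = 20% gives x = 8.8 days; m = 10% gives x = 9.4 days. The arm with fewer deaths looks 9.4 − 8.8 = 0.6 days worse.
- 30% against 20% gives 8.2 against 8.8 days, again 0.6.
- 25% against 20% gives a difference of 0.3 days.
- Equal mortality (10%, 20% or 30% in both arms) gives a difference of about zero.

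If death is ranked worse than any stay, the median solves (1 − m)·Φ[ln(x/10)/0.8] = 0.5. This gives 12.9 days at m = 20% and 11.2 days at m = 10%, and the direction reverses.

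**Barthel index.** At assumed Day 28 mortality of 10%, 20% or 30%, 200·m = 20, 40 or 60 of the 200 patients have no Barthel value because they died.

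**The case against.** The case against is substantial, and most of it stands.

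*An unadjusted comparison is not an error.* Correct. Randomisation makes it unbiased, and its interval already allows for chance baseline imbalance. A reader might infer that omitting the baseline value biases the laboratory results; it does not. The point is efficiency only.

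*The baseline analytes are unconfirmed.* Also correct. The article says only that laboratory tests are collected and refers to S1 Table. Transthyretin or the lipids may not be measured at entry, so the proposal must be limited to analytes that are.

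*The plan does not say what happens to deaths.* A reader might infer that it counts death as a short stay, or compares the Barthel index in survivors only. No sentence says so. These are what the stated methods would give if nothing else were specified, and the article is a condensed account whose full protocol and any SAP are not shown. The missing rule alone is therefore no finding. What remains is that the comparison, as stated, is vulnerable if mortality differs.

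*A mortality difference is not expected.* Nothing in the documents anticipates one from a formula given for 3 days and at most 7. Survival on Day 28 is itself reported, so an imbalance would be seen beside the stays. This limits the weight of the second point.

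*Free-day endpoints with death scored 0, and a Barthel score of 0 for death, would be the obvious repair.* Neither is required. Replacing stay by free days changes the endpoint, which is debatable. A Barthel score of 0 would tie a death with a living, fully dependent patient.

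**Conclusion.** The point holds as a modest improvement to secondary analyses. The main part is precision: the stated laboratory comparison is valid, but baseline adjustment would cut interval width by about 5% to 29% for assumed correlations of 0.3 to 0.7, wherever a baseline value exists. Adjustment does not recover Day 7 or Day 14 values lost to death or discharge. That loss deserves attention, since the retention section describes observation as confined to the ICU stay.

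The second part is conditional. If mortality or its timing differs between arms, raw stay, ventilator days and the Barthel index can favour the arm with more deaths: by about 0.6 days in median stay for a 10-point difference on the assumed distributions, and by about nothing at equal mortality. The documents do not support the stronger statement that the plan adopts a wrong rule for deaths. The primary analysis, the 93 per arm and the target of 200 stand.

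**What to change.** 1. Compare each Day 7 and Day 14 laboratory endpoint that has a baseline measurement by ANCOVA, with treatment, the baseline value and hospital (the randomisation stratum) in the model. Use the log scale for skewed markers such as C reactive protein and triglycerides, and report ratios of geometric means. Endpoints without a baseline value keep the stated comparison. Give the number of patients with values in each arm at each day, because adjustment does not address those who died or were discharged.
2. Add a supportive rank-based comparison for ICU stay, hospital stay, ventilator days and the Day 28 Barthel index, with death ranked below every survivor value. For the Barthel index this means below a living patient scoring 0, not tied with one.
3. Keep the raw stays and ventilator days as description, separately for survivors and non-survivors.

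If the full protocol or SAP already contains such rules, confirming them is enough. Otherwise the cost is a few lines in the SAP, best settled before analysis begins, because the data analysts are not blinded. Survival to Day 28 is already an outcome. Ranking hospital stay also needs vital status at discharge for patients who stay longer than that, so the sponsor should check that it is recorded.
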